### Outcome measures

Demographic information will be collected at baseline, including their gender, age, education, income, marital status, medical history, medication, and types of traumatic events. Primary and secondary outcomes will be collected by a research assistant who is blinded to the group assignment at T0, T1 and T2 through questionnaires. In addition, participants from both groups will be asked to fill out a course evaluation at T1. Participants assigned to MBCT will fill out an extra section on their questionnaire indicating their mindfulness practice habits at T1 and T2. The primary and secondary outcome measures are shown below.

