### Randomization, concealment and blindness

Participants are randomised to either MBCT or Seeking Safety on 1:1 ratio. Randomisation is stratified by gender and psychiatric medication use. Randomisation results will be generated by an independent statistician with a computer and sequences are sealed in opaque envelopes by another research assistant who is not involved in the study. Participants will be informed by the research team of their allocated group based on the results in the sealed envelopes prepared beforehand. Participants will not be allowed to switch to another intervention group. Statisticians who analyse the results will be kept blinded from the group assignment.

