### Primary outcome

PCL-5 score at T1 is the primary outcome of this study. PCL-5 has four subscales and each corresponds to one DSM-5 symptoms cluster in PTSD, including intrusion, avoidance, negative alternations in cognition and mood, and alternations in arousal and reactivity [56]. It is a self-report measure that reflects the PTSD symptoms severity of participants on a Likert scale from 0 to 4, ranging from “not at all” to “extremely”. A total score could be obtained by simply summing up all 20 items. Participants who score equal to or higher than 31 are considered to display significant symptoms [53, 57]. The Chinese Version of PCL-5 is translated by Fung et al. with good internal consistency and reliability [58].

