### Statistical analysis

Statistical analysis will be conducted by a statistician blinded to the group assignment of participants. The study results will be presented according to the Consolidated Standards of Reporting Trial 10 (CONSORT-10) standards. The mean, median, standard deviation (SD), interquartile range (IQR) and 95% confidence interval (95% CI) will be presented in the data description. The analysis of covariance (ANCOVA) will be the primary analysis for the primary outcome (PCL-5) and other secondary outcomes (i.e., PHQ-9, BAI, ACS, AAQ-II, RRS, FFMQ, SCSQ), with T1 score as the outcome and T0 score as the covariate. Both intention-to-treat and per-protocol analyses will be performed. For per-protocol analysis, participants who attend more than 4 classes will be considered to have satisfactory compliance. Effect size estimates will be obtained by comparing the T0 and T1 scores mean and SD, both between and within groups. For the secondary analysis, we will apply linear mixed model (LLM) to compare changes over time for PCL-5 score and other secondary outcomes between the intervention group and the active control group. Missing data will be incorporated into the LLM based on full information maximum likelihood. Mediation analysis will be done using the Baron and Kenny mediation method and structural equation modelling (SEM). The analysis will explore if the effect of mindfulness on PTSD symptoms is mediated by rumination, experimental avoidance and attentional control.

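### An MBCT-only section on the T1 and T2 questionnaire leaves the stated blinding of the research assistant unsecured at those visits, including the primary time point

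*Protocol article*

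**What the plan says.** All of this is in the Methods of the protocol article.

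- **Who collects outcomes.** Outcome measures: "Primary and secondary outcomes will be collected by a research assistant who is blinded to the group assignment at T0, T1 and T2 through questionnaires".
- **What differs by arm.** Same section: "Participants assigned to MBCT will fill out an extra section on their questionnaire indicating their mindfulness practice habits at T1 and T2". No counterpart for the Seeking Safety arm is mentioned.
- **What is common to both arms.** Same section: "participants from both groups will be asked to fill out a course evaluation at T1".
- **Who analyses.** Randomization, concealment and blindness: "Statisticians who analyse the results will be kept blinded from the group assignment". The Statistical analysis section repeats this: "Statistical analysis will be conducted by a statistician blinded to the group assignment of participants".
- **What the primary outcome is.** The PCL-5 total at T1. Of the scale, the Primary outcome section says: "It is a self-report measure that reflects the PTSD symptoms severity of participants on a Likert scale from 0 to 4".

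**The concern.** The article makes a specific claim of blinding for the person who collects the data, and then describes a form whose content depends on the arm. A section given to one arm only marks both arms: its presence points to MBCT and its absence to Seeking Safety. If the assistant also has to issue the right version, the arm is known before the participant starts the T1 outcome scales.

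Participants know which therapy they attend, so the trial relies in part on blinded handling of the questionnaires. An assistant who knows the arm cannot score the PCL-5. That assistant can still differ between arms in how blanks are queried, how items are explained, and how hard late questionnaires are pursued. Knowledge gained at T1 also lasts through the three months to T2. The final report would then claim assessor blinding that the trial's own forms contradict.

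**Working it through.** The point is not numerical. It rests on setting the statements side by side.

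**Step 1. The research assistant, by time point.**

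| Time point | Stated blinding of the assistant | MBCT-only section on the questionnaire | Consistent as written? |
|---|---|---|---|
| T0 | yes | no | yes |
| T1 (primary) | yes | yes | no |
| T2 | yes | yes | no |

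The article locates the practice items on the participants' questionnaire, and questionnaires are the means by which the blinded assistant collects the outcomes. Nothing elsewhere in the article reconciles the two statements: it describes no separate form, no second collector, no sealed or online return, and no parallel section for the control arm. The course evaluation at T1 goes to both arms, so its presence does not reveal the arm.

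**Step 2. How many forms are involved.** Inputs from the Sample size section: 80 per arm, effect size 0.5, two-sided 5% alpha, 80% power, 20% dropout. The planned size reproduces: a two-sample t-test needs 63.77, so 64 per arm; 64 / (1 − 0.20) = 80 per arm, 160 in total. With 20% dropout, 80 × 0.80 = 64 forms per arm are returned and 80 − 64 = 16 per arm are lost. The article expects that dropout at the end and does not split it between T1 and T2. So between 64 and 80 MBCT forms would carry the section at T1, and about 64 at T2 if dropout is equal in the two arms. The same numbers of control forms would lack it. These are counts of distinguishable forms, not a measure of bias.

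**Step 3. Routes to the primary outcome.** Because the PCL-5 is a self-completed sum of items, the assistant contributes no rating. The remaining routes are prompting, help with items, and effort to retrieve questionnaires. The last bears on the 16 or so per arm expected to be lost. The article gives no information from which the size of any of these could be derived.

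**Step 4. The statistician.** The variables named for analysis are the PCL-5 and "other secondary outcomes (i.e., PHQ-9, BAI, ACS, AAQ-II, RRS, FFMQ, SCSQ), with T1 score as the outcome and T0 score as the covariate". Practice habits are not among them. The mediation analysis uses rumination, avoidance and attentional control, and per-protocol status uses attendance; neither needs the practice items. If the T1 and T2 questionnaire data were passed on whole, fields filled in one arm and empty in the other would identify MBCT even under coded labels. If those fields were held back, they would not. The article does not say which will happen.

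**The case against.** The strongest defence is that the article says only that questionnaires are used. It does not say whether they are on paper or online, handed over or sealed, or who enters the data. With online completion or sealed return, a conditional section need never be seen by the assistant. That is fair, and it means that unmasking of everyone who touches the form is not established. It does not remove the problem, because no such arrangement is described and the two statements conflict as they stand. This is a conflict between stated procedures, not a detail left to a fuller document.

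A second defence is that the impact is small, since participants know their arm anyway and score the PCL-5 themselves. This largely stands and limits the weight of the point.

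Two stronger readings are tempting, and the article supports neither. A reader might infer that the statistician is certainly unmasked. That requires the practice fields to be in the analysis file, which is not stated, and the planned analyses do not need them. A reader might also infer that blinded handling and analysis are the only safeguards left. The article also gives opaque sealed envelopes, an active control matched on group size and on number and length of sessions, a named primary outcome and time point, a named ANCOVA model and an intention-to-treat analysis. These narrow the room for arm-aware analysis choices. They do not close it: the Discussion leaves open how other interventions and mental health diagnoses will be taken into account.

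**Conclusion.** The point holds for the research assistant. As written, the stated assessor blinding is not secured at T1 and T2, and T0 is unaffected. This assumes that the assistant hands out or sees the completed form, which is the plain reading of the text. For the statistician there is only a conditional risk, which depends on a data-transfer rule that the article does not give.

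The importance is moderate. A stated safeguard is undercut at the primary time point, but the likely effect on a self-reported outcome is limited and cannot be quantified from the document. The point does not affect the sample size, the choice of endpoint or the primary model.

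**What to change.** Choose one of two arrangements before T1 collection:

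1. Give both arms one identical section on home use of course skills, worded neutrally. This is feasible, since the control arm also has materials for use between sessions (a coping sheet and a recovery commitment form). Answers could still hint at the arm, so the section should follow the outcome scales.
2. Move the mindfulness-practice items to a separate form, completed after the outcome scales and returned to existing team members who already know allocation. Such members exist, because the research team tells participants their group.

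Under either option, withhold the practice fields from the blinded statistician's file until the primary analysis is locked, and say so in the text. If neither is adopted, withdraw the claim that the research assistant is blinded at T1 and T2.

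The cost is one reformatted form and one data-transfer rule, with no new staff or visits. The small downside is that practice data are linked to outcomes later.

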### Primary outcome

PCL-5 score at T1 is the primary outcome of this study. PCL-5 has four subscales and each corresponds to one DSM-5 symptoms cluster in PTSD, including intrusion, avoidance, negative alternations in cognition and mood, and alternations in arousal and reactivity [56]. It is a self-report measure that reflects the PTSD symptoms severity of participants on a Likert scale from 0 to 4, ranging from “not at all” to “extremely”. A total score could be obtained by simply summing up all 20 items. Participants who score equal to or higher than 31 are considered to display significant symptoms [53, 57]. The Chinese Version of PCL-5 is translated by Fung et al. with good internal consistency and reliability [58].

### Secondary outcomes

Patient Health Questionnaire-9 (PHQ-9) is used to measure the depressive symptoms of participants. It consists of 9 items total and a score could be obtained by simple summation. The cut-off scores for mild, moderate, moderately severe and severe depression are 5, 10, 15 and 20 respectively [59].

The Beck Anxiety Inventory (BAI) is used to measure the anxiety symptoms of participants [60]. It is a self-report measure with 21 items, consisting of the different symptoms that one might experience during anxiety. A total score could be obtained by adding up the items. The cut-off of 8, 16 and 26 represents mild, moderate and severe anxiety respectively [61]. The Chinese version of BAI has satisfactory internal consistency [62].

Attentional Control Scale (ACS) is used to measure attentional control [63]. It consists of 2 subscales which measure the 2 components of attention, including attention focusing and attention shifting. There are 20 items in total on a 4-point Likert scale, ranging from “almost never” to “always”.

Experimental avoidance is measured by Acceptance and Action Questionnaire-II (AAQ-II) [64]. The Chinese Version is validated with satisfactory reliability [65]. Psychological flexibility refers to the tendency to suppress or avoid negative thoughts, feelings, or emotions. It is a 7-point Likert scale ranging from 0 to 7, representing “never true” to “always true”.

Rumination is measured by the Rumination Response Scale (RRS). It consists of 22 items ranging from 0 to 4, representing “never” to “always”. The Chinese Version is validated with a higher internal consistency and reliability [66].

Mindfulness is measured by the Five-Facet Mindfulness Questionnaire (FFMQ). There are 20 items consisting of 5 subscales, which include observing, describing, acting with awareness, non-judgement and non-reaction. The Chinese Version of FFMQ has been validated by our team in prior studies, demonstrating a high internal consistency and reliability [67].

Coping Skills is measured by the 20-item Simplified Coping Style Questionnaire (SCSQ). The scale consists of 2 subscales, positive coping style and negative coping style. It is on a 4-point Likert scale, ranging from “never” to “very often”. It was originally developed from the Ways of Coping Questionnaire by Folkman and Lazarus. The SCSQ demonstrates good internal consistency and reliability [68].

### Statistical analysis

Statistical analysis will be conducted by a statistician blinded to the group assignment of participants. The study results will be presented according to the Consolidated Standards of Reporting Trial 10 (CONSORT-10) standards. The mean, median, standard deviation (SD), interquartile range (IQR) and 95% confidence interval (95% CI) will be presented in the data description. The analysis of covariance (ANCOVA) will be the primary analysis for the primary outcome (PCL-5) and other secondary outcomes (i.e., PHQ-9, BAI, ACS, AAQ-II, RRS, FFMQ, SCSQ), with T1 score as the outcome and T0 score as the covariate. Both intention-to-treat and per-protocol analyses will be performed. For per-protocol analysis, participants who attend more than 4 classes will be considered to have satisfactory compliance. Effect size estimates will be obtained by comparing the T0 and T1 scores mean and SD, both between and within groups. For the secondary analysis, we will apply linear mixed model (LLM) to compare changes over time for PCL-5 score and other secondary outcomes between the intervention group and the active control group. Missing data will be incorporated into the LLM based on full information maximum likelihood. Mediation analysis will be done using the Baron and Kenny mediation method and structural equation modelling (SEM). The analysis will explore if the effect of mindfulness on PTSD symptoms is mediated by rumination, experimental avoidance and attentional control.

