## Introduction

Post-traumatic stress disorder (PTSD) is a psychiatric condition triggered by experiencing or witnessing a traumatic event [1]. Some examples of traumatic events are sexual assault, domestic violence, childhood abuse, serious injury, illness, transportation accidents, natural disasters, or any stressful events that threaten personal lives or those of their close ones [2]. The major symptoms of PTSD include flashbacks of traumatic events, sleep disturbance, nightmares, rumination, negative thoughts, avoidance, and dysregulated hyperarousal [3]. While exposure to trauma is common, only a minority will develop and meet the full diagnostic criteria of PTSD [4]. Subthreshold PTSD refers to the condition in which only part of the symptoms are present clinically. While this condition does not fulfill the diagnosis of PTSD, it is found to be more prevalent in the community [4]. A study in 2014 conducted across 24 countries found that while 3% of participants met the diagnostic criteria of DSM-5 for PTSD, there was an additional 4.6% that met the criteria of subthreshold PTSD [4]. In general, these people experience symptoms that are less intense than full PTSD. However, their impairment is still significant to well-being and everyday life [5]. Zlotnick et al. found no significant differences in terms of functional impairment between patients with full PTSD and subthreshold PTSD, suggesting that people with subthreshold PTSD could experience negative impacts comparable to that of a full PTSD condition [6]. Other studies showed diminished social and family functioning [7], more days of absence from work [8], and a greater risk of suicidal ideation among subthreshold PTSD patients [9]. Besides, co-morbidity of mental health disorders, such as eating disorders, major depressive disorder, general anxiety disorder, and substance abuse are common among individuals with subthreshold PTSD [10]. Yet, some studies found that veterans with subthreshold PTSD did not utilize mental health services more than those with no PTSD, despite their significant impairment [11]. Another study on elderly with subthreshold PTSD found that they were more likely to perceive the care they received as inadequate [12]. These suggest that subthreshold PTSD might be easily overlooked by clinicians. Hence, subthreshold PTSD should be considered a condition that requires clinical attention and intervention.

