#### Hypotheses

MBCT is more effective in reducing PTSD symptoms when compared to Seeking Safety, the active control group;MBCT is more effective in reducing depressive and anxiety symptoms when compared to Seeking Safety, the active control group.Attentional control, avoidance and ruminative thoughts are the mediators of MBCT in reducing PTSD symptoms in MBCT.

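### Avoidance is both a hypothesised mediator (AAQ-II) and a subscale of the PCL-5 total, so the indirect effect through AAQ-II may be inflated

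*Protocol article*

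**What the plan says.** All references are to the protocol article.

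- **Hypotheses:** "Attentional control, avoidance and ruminative thoughts are the mediators of MBCT in reducing PTSD symptoms in MBCT".
- **Statistical analysis:** "The analysis will explore if the effect of mindfulness on PTSD symptoms is mediated by rumination, experimental avoidance and attentional control". The methods named are Baron and Kenny and structural equation modelling.
- **Secondary outcomes:** the avoidance mediator is measured by the AAQ-II. The construct in that paragraph is described as "the tendency to suppress or avoid negative thoughts, feelings, or emotions". Rumination is measured by a separate scale, the RRS.
- **Primary outcome:** the PCL-5 has four subscales, "including intrusion, avoidance, negative alternations in cognition and mood, and alternations in arousal and reactivity". On scoring: "A total score could be obtained by simply summing up all 20 items".
- **Abstract:** PTSD symptoms, as the primary outcome, are tied to the PCL-5. The article names no other measure of PTSD symptoms.
- **Introduction:** "The major symptoms of PTSD include flashbacks of traumatic events, sleep disturbance, nightmares, rumination, negative thoughts, avoidance, and dysregulated hyperarousal".

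The article does not say how the avoidance mediator will be kept apart from the avoidance items in the outcome.

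**The concern.** A mediation analysis asks whether treatment changes the mediator and whether that change carries the effect to the outcome. If part of the outcome score measures the same content as the mediator, the two are associated even when the mediator influences no other symptom. Some of that association is then read as an indirect effect.

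Here the avoidance items are summed into the PCL-5 total, and AAQ-II is proposed as an explanation of change in that total. The third hypothesis is at stake, together with the strength claimed in the Discussion that studying mediators will clarify how the intervention works. The avoidance part of that hypothesis could appear confirmed more often, or with a larger mediated share, than the data justify.

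**Working it through.** **Design figure.** The article gives no figure for the mediation analysis. Its only design figure is N = 160. A two-sample t-test with d = 0.5, two-sided 5% error and 80% power needs 64 per arm. With 20% dropout, 64 / 0.80 = 80 per arm, or 160 in total. This reproduces exactly. The 64 completers per arm are used in the simulation below.

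**Model with no true mediation.** Let A be the avoidance content of the PCL-5, B the remaining symptoms and M the AAQ-II, each with unit variance within arm.

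- M correlates r with A and has no effect on any symptom.
- A and B correlate ρ within arm.
- k of the 20 items carry A, so Y = kA + (20 − k)B.
- Treatment shifts A and B equally, by d.

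The article gives the 20 items, the four subscales and d = 0.5. It does not give k, r or ρ, so these are assumptions.

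- Path a (treatment to M) = r·d
- Path b (M to Y given treatment) = r·[k + (20 − k)ρ]
- Total effect = 20·d
- Apparent mediated share = a·b / total = r²·[k + (20 − k)ρ] / 20

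**Independent symptoms (ρ = 0).** The share reduces to k·r²/20.

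| k | r = 0.5 | r = 0.7 | r = 1.0 |
|---|---|---|---|
| 2 | 2.5% | 4.9% | 10% |
| 5 | 6.2% | 12.2% | 25% |

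The value k = 5 is what an even split of 20 items over four subscales would give. It is not stated in the article.

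A simulation of 2,000 trials with 64 completers per arm agreed (5.1% and 12.4% at r = 0.7). Both paths were significant in 8% of trials for k = 2 and 36% for k = 5, against 2% with no overlap.

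**Correlated symptoms (ρ = 0.5, r = 0.7).**

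- k = 0: 0.49 × 10/20 = 24.5%
- k = 2: 0.49 × (2 + 9)/20 = 27.0%
- k = 5: 0.49 × (5 + 7.5)/20 = 30.6%

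Overlap therefore adds about 2.5 points (k = 2) or 6 points (k = 5) to a spurious share that is already there. In simulation, both paths were significant in about half of trials whether or not items overlapped (50%, 51% and 51% for k = 0, 2 and 5).

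**After removing the avoidance items.** The outcome is (20 − k)B, and the share becomes r²·ρ. That is 0 at ρ = 0 and 0.49 × 0.5 = 24.5% at ρ = 0.5. Removal eliminates the overlap component and nothing else.

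**Effect confined to avoidance.** If treatment moves only A and ρ = 0, the share is r² = 0.49. The total effect is then small, however. With avoidance carrying 10% of the score weight, the standardised effect is 0.05 / √(0.1² + 0.9²) ≈ 0.055. With 25%, it is 0.125 / √(0.25² + 0.75²) ≈ 0.16. Power to detect these with 64 per arm is roughly 6% and 15%.

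**The case against.** **Separate instruments.** AAQ-II and PCL-5 are different scales, and general avoidance of inner experience is not stated to be identical to the PCL-5 avoidance cluster. The sentence describing the AAQ-II construct is also garbled, since its subject is psychological flexibility, so it is weak evidence of item content. This stands. A reader might infer that one symptom is simply measured twice, so that both scores fall together by construction. The documents support overlap in content, not identity.

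**Rumination.** A reader might extend the point to the RRS, because the Introduction lists rumination among PTSD symptoms. The Primary outcome section does not name rumination as a PCL-5 subscale or item. Placing it under negative cognition and mood is an inference, so the point does not extend to rumination.

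**Confounding dominates.** Independent symptom clusters are hard to square with the good internal consistency the article reports for the PCL-5. Once symptoms correlate, most of the spurious share comes from ordinary mediator-outcome confounding. This also stands. It rules out treating persistence on the reduced score as proof of mediation, and it argues against a strict rule that mediation may be claimed only on that score.

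**Method and timing.** Nothing shows that overlap survives every method or time lag. A structural equation model with cluster-level outcomes, or a lagged model using T2, could reduce it. The article commits to neither.

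**Scope.** The analysis is exploratory, the article is condensed, and model detail may sit in an analysis plan that is not shown. This limits the weight of the point. Even so, the article itself fixes the mediators, the instruments and the outcome measure, and for avoidance they overlap as stated.

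**Conclusion.** The point holds for avoidance, as a modest and inexpensive improvement. Avoidance is a stated mediator and a component of the score that measures PTSD symptoms, so the indirect effect through AAQ-II may be inflated.

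With equal treatment effects and independent symptoms, overlap alone yields an apparent mediated share of about 2.5% to 10% for two overlapping items. With symptoms correlated within arm it adds only a few points. These figures rest on assumed values of k, r and ρ. The larger results, such as 36% of trials with both paths significant or about half of the effect appearing mediated, need either five overlapping items or an effect confined to avoidance, and the documents establish neither.

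Only the third objective is touched. The primary ANCOVA on the PCL-5 at T1 and N = 160 stand as planned.

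**What to change.** In the Statistical analysis section, pre-specify for AAQ-II a mediation analysis whose outcome is the PCL-5 total minus its avoidance subscale. Report it beside the model on the full total, and word the conclusion on the avoidance mechanism cautiously if the indirect effect does not persist. The primary outcome remains the full PCL-5 total.

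A parallel analysis for the RRS without the negative cognition and mood subscale may be added as an optional sensitivity analysis. The documents do not require it.

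The cost is a few lines of text, using items already collected. The shorter outcome score will be slightly less reliable in that one model. The change does not remove ordinary mediator-outcome confounding, and the text should say so.
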